## Abstract

**Background:**

Metastasis-directed therapy (MDT) significantly delays the initiation of palliative androgen deprivation therapy (pADT) in patients with oligorecurrent prostate cancer (PCa) with a positive impact on patient’s quality of life. However, it remains unclear whether the addition of ADT improves polymetastatic free survival (PMFS) and metastatic castration refractory PCa-free survival (mCRPC-FS) and how long concomitant hormone therapy should be given. A significant overall survival (OS) benefit was shown when an androgen receptor targeted agent (ARTA) was added to pADT in patients with metastatic hormone sensitive PCa (HSPC). However, whether the addition of and ARTA to MDT in the treatment of oligorecurrent PCa results in better PMFS and mCRPC-FS has not been proven yet.

**Methods & design:**

Patients diagnosed with oligorecurrent HSPC (defined as a maximum of 5 extracranial metastases on PSMA PET-CT) will be randomized in a 1:1:1 allocation ratio between arm A: MDT alone, arm B: MDT with 1 month ADT, or arm C: MDT with 6 months ADT together with ARTA (enzalutamide 4 × 40 mg daily) for 6 months. Patients will be stratified by PSA doubling time (≤ 3 vs. > 3 months), number of metastases (1 vs. > 1) and initial localization of metastases (M1a vs. M1b and/or M1c). The primary endpoint is PMFS, and the secondary endpoints include mCRPC-FS, biochemical relapse-free survival (bRFS), clinical progression free survival (cPFS), cancer specific survival (CSS), overall survival (OS), quality of life (QOL) and toxicity.

**Discussion:**

This is the first prospective multicentre randomized phase III trial that investigates whether the addition of short-term ADT during 1 month or short-term ADT during 6 months together with an ARTA to MDT significantly prolongs PMFS and/or mCRPC-FS.

**Trial registration:**

ClinicalTrials.gov Identifier: NCT05352178, registered April 28, 2022.

## Background

### Metastasis-directed therapy

Up to 50% of patients treated with curative intent for high-risk prostate cancer (PCa) will eventually develop biochemical recurrence (BCR) at long-term follow-up [1, 2]. BCR is a precursor for the development of distant metastases and a predictor of PCa-related death. With the introduction of more sensitive imaging modalities such as prostate-specific membrane antigen (PSMA) positron emission tomography/computed tomography (PET/CT) or positron emission tomography/magnetic resonance imaging (PET/MRI) at the time of BCR, more patients are currently diagnosed with a limited number of metastases, a disease state defined as oligometastatic and in general pragmatically defined as the development of maximally 5 metastatic spots at one point in time [3]. More specific, in this setting, this disease status has been termed oligorecurrent PCa and has a different prognosis in comparison to polymetastatic PCa. Indeed, it has been demonstrated that the number of metastases is an important prognostic factor for PCa-specific survival (PCSS) [4–6]. The optimal treatment strategy in patients presenting with oligorecurrent PCa is still a matter of debate [7, 8]. While historically, palliative androgen-deprivation (pADT) therapy has been considered a state-of-the-art treatment, the advent of metastasis-directed therapy (MDT), performed by either metastasectomy or stereotactic body radiation therapy (SBRT) has broadened the therapeutic window as it significantly delays the initiation of pADT and its substantial side-effects when compared to active surveillance [9]. Retrospective studies served as a solid back-up demonstrating that the initiation of pADT could be delayed for several years which positively impacts patient’s quality-of-life (QOL) [9, 10]. Moreover, in some patients, the early use of pADT might promote the development of the castrate-resistant state, in which metastatic progression is driven by androgen-independent pathways [11].

Importantly, all the above-referred studies demonstrated that MDT using SBRT in case of oligorecurrent prostate cancer has low toxicity [9, 12, 13].

The SABR-COMET study [14] demonstrated that (for different tumor types, 21% of them being PCa patients) adding SBRT on top of the palliative systemic treatment in patients with a low-volume metastatic recurrence after previous treatment of the primary tumour significantly improved overall survival (OS) when compared to palliative systemic treatment alone. The eight-year OS was 27.2% in the SABR arm vs. 13.6% in the control arm (HR 0.5, 95% CI 0.3–0.84, *p* = 0.008) [15].

Our own research team published long-term outcomes of one of the largest retrospective analyses on MDT for oligorecurrent PCa after radical prostatectomy. In total, 191 oligorecurrent PCa patients were analysed. Estimated median palliative-ADT free survival was 66 months and estimated median mCRPC-free survival was not reached, but 83% of patients were still free of mCRPC at 10 years. In total, 314 MDTs were performed, and 25 patients (13%) received ≥ 3 MDTs. Repeated MDT resulted in low toxicity and could be offered to well-informed and motivated patients [13].

### Combining MDT with ADT

ADT has a radio-sensitizing effect by inhibiting the androgen receptor-mediated repair of radiotherapy (RT)-induced DNA damage in the PCa cells [16]. The addition of a non-timeless period of ADT to primary RT has shown to improve OS for intermediate- and high-risk PCa [17, 18]. Two recent trials also suggested a progression-free by adding temporary ADT to salvage RT, especially among young and fit patients [19, 20]. Vice-versa, the addition of RT to ADT improved OS in patients presenting with high-risk disease and patients presenting with pelvic nodal disease [21–25].

When SBRT for oligorecurrent disease is applied, it is not clear whether adding ADT for a certain period will extend the postponement of polymetastatic disease and the development of mCRPC. Scientific reports on MDT in PCa so far use SBRT as monotherapy or in combination with a certain period of ADT [12, 13, 26, 27].

### Combining ADT with second-line hormonal therapy

In three large randomized controlled trials (ENZAMET [28], ARCHES [29] and TITAN [30]), the addition of an androgen receptor targeted agent (ARTA) to ADT in men with metastatic hormone-sensitive PCa (mHSPC) was tested [28, 29, 31]. In ARCHES, the primary endpoint was radiographic progression-free survival (rPFS). rPFS was significantly improved when enzalutamide was added to ADT with a HR of 0.39 (0.3–0.5; *p* < 0.001). Approximately 36% of patients included in this trial had low-volume metastatic disease [29]. Recently the analysis of the secondary endpoints was published and concluded that the combination of enzalutamide with ADT reduced risk of death by 34% with a HR of 0.66 (0.53–0.81; *p* < 0.001) [32]. In the ENZAMET trial, the primary endpoint was overall survival (OS). The addition of enzalutamide to ADT improved OS with a HR of 0.67 (0.52–0.86; *p* = 0.002). Approximately half of the patients had low volume metastatic disease [28]. In the TITAN trial, apalutamide was added to ADT. The endpoints were rPFS and OS. rPFS was significantly improved in the combination group with a HR of 0.48 (0.39–0.60; *p* < 0.001). OS at 24 months was improved for the combination with a HR of 0.67 (0.51–0.89; *p* < 0.005). In this trial, 37% of patients had low volume metastatic disease [31]. In summary, all these trials resulted in the same conclusion: the addition of ARTA to ADT significantly improves clinical outcomes.

In two other large randomized controlled trials (STAMPEDE [33] and LATITUDE [34]), the addition of abiraterone acetate plus prednisone to ADT in men with mHSPC at first presentation was studied. Both trials showed a significant improvement in OS with a HR of 0.61 (0.53–0.70; *p* < 0.001) in the subgroup analysis for mHSPC in the STAMPEDE trial and a HR of 0.62 (0.51–0.76; *p* < 0,001) in the LATITUDE trial [33, 34]. Finally, the androgen receptor inhibitor, darolutamide, was tested in the ARASENS trial [35] in combination with ADT, and docetaxel among patients with mHSPC with OS as primary endpoint. The OS was significantly improved in the combination group with darolutamide with a HR of 0.68 (0.57–0.80; *p* < 0,001) [35].

But, although a substantial number of patients in the above-mentioned studies had low-volume metastatic disease, none of them examined the combination treatment of SBRT along with ADT and ARTA.

## Methods/design

### Study design

SPARKLE (a new **S**park in treating oligorecurrent **P**rostate cancer: **A**dding systemic treatment to stereotactic body **R**adiotherapy or metastasectomy: **K**ey to **L**ong-lasting **E**vent-free survival?) is approved by the Ethics committee of the Leuven University Hospitals (LUH) (EC2022/S65935) and is registered at the EudraCT data base (2022–000,066-18) and at clinicaltrials.gov (NCT05352178). It is a prospective, multicenter, randomized, open-label, three-arm, phase III study. The aim is to investigate whether the addition of short-term ADT during 1 month or short-term ADT during 6 months together with an ARTA to MDT significantly prologs polymetastatic-free survival (PMFS). The following arms will be compared (1:1:1) (Fig. 1):1. Arm A: MDT alone2. Arm B: MDT + 1 month of ADT3. Arm C: MDT + 6 months of ADT together with 6 months ARTA (enzalutamide)

**Fig. 1 Fig1:**
[figure not shown]
Trial design BcR: Biochemical recurrence; OligoM + : oligometastatic disease; PSMA PET-CT/MRI: prostate-specific membrane antigen (PSMA) positron emission tomography/computed tomography (PET/CT) or positron emission tomography/magnetic resonance imaging (PET/MRI); T: testosterone; PSA: prostate specific antigen; M1a: non-regional lymph node metastases, M1b: bone metastases, M1c: visceral metastases; SBRT: stereotactic body radiotherapy; ADT: androgen deprivation therapy

The primary endpoint is polymetastatic-free survival (PMFS).

### Inclusion criteria

All patients must fulfil the following inclusion criteria:• Histologically proven initial diagnosis of prostatic adenocarcinoma.• Prior treated and controlled primary tumor. Patients with local recurrence can be included only when accompanied by M1a-c disease, provided that the total number of active lesions does not exceed 5.• Biochemical recurrence defined by prostate-specific antigen (PSA) values > 0.2 ng/ml (i.e., two consecutive increases) following radical prostatectomy ± postoperative RT and a PSA value of 2 ng/ml above the nadir after high-dose RT and confirmed at least once [36].• Presence of oligorecurrent disease defined as a maximum of 5 extracranial metastases in any organ, diagnosed on PSMA PET-CT (PSMA PET-MRI is allowed, but optional) reported according to the E-PSMA consensus guidelines for interpretation of PSMA-PET [37]. Nodal (N1) disease can be included only when accompanied by M1a-c disease, provided that the total number of active lesions does not exceed 5.• Serum testosterone level within normal range.• WHO performance 0–2.• Age >  = 18 years old.• Willing to provide a signed informed consent.• Absence of psychological, sociological, or geographical condition potentially hampering compliance with study protocol.• Patients must be presented at the multidisciplinary board meeting and the inclusion in the trial needs approval by this board.

### Exclusion criteria

• Serum testosterone level at castration level.• PSA rise while on active treatment (LHRH-agonist, LHRH antagonist, anti-androgen, maximal androgen blockade, oestrogens).• Presence of poly-metastatic disease, defined as more than 5 extracranial metastatic lesions visible on PSMA PET-CT.• Pelvic nodal disease (N1) without the presence of metastatic disease (M1a-c).• Active malignancy other than prostate cancer that could potentially interfere with the interpretation of this trial (decision left to the principal investigator).• Previous treatments (RT, surgery) or comorbidities rendering new treatment with SBRT or metastasectomy impossible.• Contraindications for intake of enzalutamide (seizure or any condition that may predispose to seizure; significant cardiovascular disease within the last three months including myocardial infarction, unstable angina, congestive heart failure, ongoing arrythmias of grade > 2 or a thromboembolic event).• Not able to understand the treatment protocol or sign the informed consent.

### Evaluation and randomization

Patients must be staged with PSMA PET-CT/MRI within 4 weeks prior to randomization. The study will employ a 1:1:1 randomization between arm A: arm B: arm C. Patients will be stratified according to PSA doubling time (≤ 3 vs. > 3 months), number of metastases (1 versus > 1) and initial localization of metastases (M1a vs. M1b and/or M1c) (Fig. 1). Randomization will be performed centrally at the University Hospitals Leuven.

### Interventions

All patients eligible for the trial will be recruited after a mandatory discussion on the multidisciplinary urology tumour board, and after approval from the attending physician if a patients is referred from another external treatment centre. Leuven University Hospitals has started recruitment in April 2022. Participating treatment centres will be added subsequently following the legal ethical requirements i.e. starting at least 3 months after inclusion of the first patient in Leuven University Hospitals. After being considered eligible, the patient will follow the trial procedure. At first, a screen visit is scheduled, on which the patient will receive a standard clinical examination and laboratory analysis including peripheral blood cell count with formula, liver and kidney function, alkaline phosphatase, lactate dehydrogenase, PSA and testosterone. Three Quality-of-life questionnaire (QLQ-30, QLQ-PR25 and EQ-5D) [38, 39] as well as a toxicity score will be carried out [40] after signature of the informed consent. Post-treatment follow-up will be planned according to the trial protocol: there are 5 follow-up visits (month 1 and further on 3-monthly basis) scheduled in year 1 and 3-monthly follow-up visits thereafter unless clinical evolution requires more monitoring. The timeline of the participants is shown in Fig. 2. The summary of the study visits is displayers in Table 1.

**Fig. 2 Fig2:**
[figure not shown]
Participants timeline. Timeline depending on study arm and follow-up schedule

**Table 1 Tab1:** Trial flowchart

Preliminary investigations	Radiotherapy:	
	‐ CT-simulation	
	‐ MRI for radiotherapy planning	
	‐ **Completing the questionnaire**	
	Surgery:	
	‐ Pre-operative consultation anesthesia	
	‐ **Completing the questionnaire**	
Start hormone therapy (14 days before the metastasis-directed therapy)	Group A	/
	Group B	start hormone therapy for 1 month
	Group C	start first-line hormone therapy + second-line hormone therapy for 6 months
Metastasis-directed therapy	- Surgery - Radiotherapy: 3–7 irradiation treatments, max 3x/week	
End of Radiotherapy	- Standard follow-up + blood sample + **completing the questionnaire**	
Month 1	- Standard follow-up + blood sample + **completing the questionnaire**	
Month 3		
Month 6		
Month 9 and every 3 months thereafter	- Standard follow-up + blood sample + **completing the questionnaire at month 12 and 24**	

Summary of study visits and procedures

### Stereotactic body radiotherapy

For the treatment with SBRT, all patients will receive a CT simulation with 1 mm CT slice thickness through the oligorecurrence site(s) and neighbouring organs at risk. In case of non-bony oligorecurrence, intravenous contrast will be applied (standard procedure). For lung lesions we recommend motion management with a 4D-CT simulation scan. The isocenter will be placed in the center of the oligorecurrent lesion (standard procedure). In order to increase patient comfort and stability, different support devices can be used depending on the location of the metastases and following the standard procedure of the participating centres. Delineation of the oligorecurrent metastatic lesion(s) as gross target volume (GTV) will be based on CT and hybrid PSMA PET imaging (PET-CT/MRI). The additional use of magnetic resonance imaging is left at the discretion of the treating team, however, is highly recommended in case of bony metastases. The GTV will be expanded to create the Planning Target Volume (PTV) with a margin that accounts for setup error and organ motion with a maximum of 7 mm. Using intensity-modulated arc therapy (IMAT) or volumetric arc therapy (VMAT), the aim is to prescribe a biologically equivalent dose (BED) of at least 100 Gy using an alpha over beta of 3. Typically, a total dose of 36 Gy will be prescribed in 3 fractions of 12 Gy. Treatment will be prescribed to the periphery of the target and (80% of the dose should cover 90% of the PTV). Dose constraints for organ at risk (OAR) will be in accordance the AAPM task group 100 report [41]. Dose constraints for OAR take precedence over the prescribed dose to the PTV. Treatment will be delivered using photons from a linear accelerator. Image-guided RT is mandatory and will be performed using daily cone-beam CT. Fractions will be separated > / = 48 h and < 72 h.

### Surgery

The surgical technique to be used is at the discretion and expertise of the surgeon but has to be in accordance with the best surgical practice available. When possible, minimally invasive techniques are preferred. A template-based lymph node dissection (LND) is preferred above removing only the suspicious node in the case of lymph node metastasis, but not mandatory. Pelvic LND is defined as the removal of lymph nodes distal to the aortic bifurcation (internal, external and obturator iliac, common iliac, perirectal and/or presacral). Retroperitoneal LND is defined as the removal of lymph nodes above the aortic bifurcation, with upper level at least 1 cm above the most cranial lesion. The surgical removal of bone metastasis or visceral metastasis will always be performed in consultation and according to the expertise of the surgeon specialized for the respective location of metastasis.

### Hormonal therapy

Androgen deprivation therapy (goserelin, leuprorelin, triptorelin, degarelix) has to be started at least 2 weeks before the RT. SBRT must be completed within the timeframe of chemical castration i.e. within 4 weeks in Arm B and within 6 months in Arm C. To prevent flare-up, bicalutamide 50 mg will also be started once daily for 1 month in case of administration of goserelin, leuprorelin or triptorelin. From the second week of bicalutamide intake, ADT can be initiated.

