### Objectives

#### Primary endpoint

◦ Poly-Metastatic Free Survival (PMFS) will be determined from the last day of the first SBRT or from the day surgery was performed until the first day of poly-progression which is defined as the detection > 5 new lesions at PSMA PET-CT/MRI (± combined with MRI if needed to improve diagnostic accuracy). In case of poly-progression, pADT combined with chemotherapy [42–44], ARTA [28, 29, 31] or abiraterone-acetate [33, 34] will be considered the standard-of-care. The decision on which treatment will be offered will be taken on the multidisciplinary meeting in every case and will take into account former treatment. If recurrence occurs in ≤ 5 lesions, a new MDT is proposed if technically feasible and the patient will receive again the treatment he was allocated to at the time of initial randomisation. Patients free from poly-progression are censored at their last follow-up.

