#### Secondary endpoints

◦ Metastatic Castration-Refractory Prostate Cancer Free Survival (mCRPC-FS) will be determined from the last day of the first SBRT or from the day surgery was performed until the first day of diagnosis of CRPC. CRPC is defined according to the contemporary EAU-guidelines as the time to biochemical and/or clinical progression at castrate testosterone levels (< 50 ng/dl). Biochemical progression is defined as three consecutive PSA rises (1 week interval), of which at least 2 rises with a PSA level of > 2 ng/ml and a rise of 50% above the nadir PSA level [45]. Patients free from CRPC are censored at their last follow-up.◦ Biochemical relapse-free survival (bRFS) will be determined from the last day of the first SBRT or from the day surgery was performed until the first day of BCR. BCR is defined as three consecutive PSA rises (1 week interval), of which at least 2 rises with a PSA level of > 2 ng/ml and a rise of 50% above the nadir PSA level. Patients free from BCR are censored at their last follow-up.◦ Clinical progression free survival (cPFS) will be determined from the last day of the first SBRT or from the day surgery was performed until the first day of clinical relapse. Patients free from clinical relapse are censored at their last follow-up. Clinical relapse is defined as the appearance of 1 new lesion with a high suspicion on PSMA PET-CT/MRI [46].◦ Cancer Specific Survival (CSS) will be determined from last day of the first SBRT or from the day surgery was performed until PCa death. Death of other causes is considered a competing event, while patients alive are censored at last follow-up.◦ Overall Survival (OS) will be determined from last day of the first SBRT or from the day metastasectomy was performed until death from any cause, with censoring of patients alive at last follow-up.◦ Acute and late toxicity score as a result of RT will be scores using the Common Toxicity Criteria Version 5.0 [47]. Toxicity will be scored at every visit during follow-up (see Table 1).◦ Quality of life scoring using the EORTC QLQ-C30 supplement with QLQ-PR25. We will assess the quality-of-life-years with the EuroQOL classification system (EQ-5D-5L). The questionnaires are administered at baseline, last day of treatment, and during follow-up consultation at month M1, M3, M6, M12 and M24 (see Table 1).

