### Statistical analysis

#### Sample size

The required sample size was based on the following considerations. We assume a delay of PMFS after MDT alone of approximately 21 months [9]. We consider an additional median delay of PMFS of 12 months in arm B and another additional 12 months of PMFS in Arm C as clinically meaningful. The sample size calculation was determined for a two-sided long-rank test for each of the three pairwise comparisons (Arm A vs. Arm B, Arm A vs. Arm C, Arm B vs. Arm C). We suppose a 5-years of accrual and a minimum of 5 years of follow-up to determine the primary endpoint with a 10% 5-year censoring (drop-out) rate. To account for multiple testing, a Bonferroni-correction was applied, implying a test-wise significance level of 0.0167, in order to keep a family-wise significance level of 5%. A sample size of 873 patients is required (291 patients in each arm) to obtain a power of at least 80% in each of the three tests.

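### The SBRT completion limit is 4 weeks in arm B but 6 months in arm C, so the permitted start of the PMFS clock can differ between these arms by up to 5.1 months; the likely effect is small and one common window would close the gap

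*Protocol article*

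**What the plan says.** The statements below are all in the protocol article.

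- **Hormonal therapy**, outer limit: "SBRT must be completed within the timeframe of chemical castration i.e. within 4 weeks in Arm B and within 6 months in Arm C". Each limit matches that arm's duration of ADT.
- **Hormonal therapy**, lead-in: ADT "has to be started at least 2 weeks before the RT". This is a minimum only.
- **Table 1 (trial flowchart)**: "Start hormone therapy (14 days before the metastasis-directed therapy", in one row that covers groups B and C alike. SBRT takes 3 to 7 sessions, at most three a week.
- **Primary endpoint**: "Poly-Metastatic Free Survival (PMFS) will be determined from the last day of the first SBRT or from the day surgery was performed".
- **Secondary endpoints**: mCRPC-FS, bRFS, cPFS and CSS use the same origin, and so does OS: "Overall Survival (OS) will be determined from last day of the first SBRT or from the day metastasectomy was performed".
- **Study design**: "It is a prospective, multicenter, randomized, open-label, three-arm, phase III study".
- **Evaluation and randomization**: "Patients must be staged with PSMA PET-CT/MRI within 4 weeks prior to randomization". This limits how old the staging scan may be at randomisation. It sets no date for MDT.

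**The concern.** The clock for the primary endpoint starts after randomisation, on a date that the treating team schedules knowing the arm. The latest permitted date, counted from hormone start, depends on the arm. A late arm C course stays within the Hormonal therapy limit, whereas the same course in arm B would breach it.

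A late time zero in arm C can act in either direction:

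- It can leave out months in which hormones hold the disease. This shortens measured PMFS and works against arm C.
- It can leave out patients who progress before MDT, so that a lower-risk group is followed. This works in favour of arm C.

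The comparison at stake is B versus C. It rests on a 12-month difference in median ("We consider an additional median delay of PMFS of 12 months in arm B and another additional 12 months of PMFS in Arm C") and has no power to spare. A versus C has so much power that a shift of this size cannot matter there.

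**Working it through.** **1. Reproduce the planned size (Sample size section).** Medians are 21, 33 and 45 months. The test is two-sided at 0.05/3 = 0.0167, with 5 years of accrual, at least 5 years of follow-up, 10% drop-out at 5 years and 291 patients per arm. Exponential PMFS is assumed.

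- B versus C hazard ratio: 33/45 = 0.733, and |ln HR| = 0.310.
- Events for 80% power (Schoenfeld): 4 × (2.394 + 0.842)² / 0.310² = 436.
- Event probability, averaged over follow-up T from 60 to 120 months: λ/(λ+γ) × (1 − e^(−(λ+γ)T)), with λ = ln 2/median and γ = −ln(0.9)/60. This gives 0.794 in B and 0.697 in C, mean 0.746.
- Patients per arm: 436 / (2 × 0.746) = 293, against the stated 291. The plan's figure is reproduced.
- At 291 per arm: 434.1 events, power Φ(√434.1/2 × 0.310 − 2.394) = 79.9%. Simulation of 8,000 trials with the log-rank test gives 79.2%.

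**2. Permitted difference in time zero.** Both limits are counted from the first ADT dose (assumption).

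- Arm B: 4 weeks = 28 days. Arm C: 6 months, taken as 182 days.
- 182 − 28 = 154 days; 154/30.44 = 5.06 months.
- This is 5.06/12 = 42% of the difference in medians on which B versus C is powered.

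**3. Difference if Table 1 is followed.** MDT starts on day 14 in both arms. With Monday/Wednesday/Friday sessions (assumption), a 3-fraction course ends on day 18 to 20, a 5-fraction course on day 23 to 25 and a 7-fraction course on day 28 to 29. The arms share this schedule, so the difference is nil.

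**4. Cost under a constant hazard with all of arm C late.** A constant hazard is memoryless, so the hazard ratio after time zero stays 0.733. Only patients and events are lost.

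- Arm C patients with an event before the late time zero: 1 − 2^(−5.06/45) = 7.5%, or 291 × 0.075 = 21.8 patients.
- If these are left out and the rest have the full planned follow-up from time zero: 434.1 − 21.8 × 0.697 = 418.9 events, power 78.2%.
- If follow-up ends at the same calendar date instead: 434.1 − 21.8 = 412.3 events, power 77.5%.
- Simulation of the first of these losses (8,000 trials) gives 78.3%, against 79.2% with none late.

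The loss is 0.9 points by simulation, and 1.7 to 2.4 points by formula, for the most extreme lateness that the text permits.

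**5. A versus C.** The hazard ratio is 21/45 = 0.467. This needs 73 events for 80% power and about 465 are expected. Simulated power is at least 99.9% with none or all of arm C late.

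**The case against.** The strongest reply is that Table 1 is the schedule, and that the Hormonal therapy limits only ensure that radiotherapy falls under castration, in line with the radiosensitising rationale in the Background. Recent staging also makes a delay of months unlikely, and nothing in the article suggests that any arm C course will be late. This stands as an argument about likelihood. It does not alter the rule: the article names a 6-month limit for arm C, and Table 1 does not withdraw it. Completion by day 28 would keep SBRT under castration in arm C as well.

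It is also fair to say that an article may leave to the full protocol a time limit for surgery and the handling of progression before MDT. The point therefore rests only on the arm-specific limit and the time origin, both of which are stated.

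A reader might infer much larger effects, and the documents do not support them:

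- **B versus C power falling to 35%.** This assumes that every arm C patient is late and that each loses the full 5.1 months from measured PMFS (HR 33/39.9 = 0.83). Nothing in the article indicates either.
- **Type I error rising from 1.6% to between 3.2% and 6.6%, in favour of arm C.** This needs all of arm C late, an assumed frailty variance of 0.5 to 1, and removal of everyone who progresses before MDT. The article prescribes no such removal and specifies intention-to-treat. Table 1 also shows no PSMA PET between hormone start and MDT at which such progression would be found.

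These are corner cases, not estimates.

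**Conclusion.** The point holds as a minor defect. The text allows the start of the clock for PMFS and the time-to-event secondary endpoints, relative to hormone start, to differ between arms B and C by up to 154 days (5.1 months), in a trial where scheduling is done with the arm known.

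There is no effect where Table 1 is followed. Where arm C courses are late, the direction is unknown. Under a constant hazard, the loss of B versus C power is about 1 to 2 points even with all of arm C late. This rests on exponential PMFS at the planned medians and on counting both limits from the first ADT dose. The share of late courses cannot be estimated from the article. A reader might conclude that the B versus C result will be biased; the documents show only that the rule leaves room for it.

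**What to change.** 1. **Hormonal therapy section: align the limit with Table 1.** Suggested wording: *In arms B and C alike, the first MDT starts no earlier than day 14 after the first ADT dose. The first SBRT course is completed, or surgery performed, by day 28; a 7-fraction course may end up to two days later. Later MDT is recorded as a timing deviation, and the patient remains in the intention-to-treat analysis.* Day 28 is the limit that arm B already has. The typical 3-fraction course meets it with more than a week to spare; the tolerance is for 7-fraction courses, which can end on day 29.
2. **Data analysis section: add a sensitivity analysis.** Count PMFS from randomisation for all randomised patients in the three arms, with any poly-progression before the first MDT as an event.

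The sensitivity analysis shows whether the result depends on MDT timing. It does not remove that dependence from the primary analysis, which keeps its origin after randomisation.

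The cost is slightly less scheduling flexibility in arm C, some timing deviations to record, and one extra analysis. Sample size, visits and the primary analysis do not change.
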